### Interventions

The intervention in this study will not involve differences in the intensity or frequency of rehabilitation; the focus will be on modifying protein intake between the two groups. In the control group, nutritional support will target the lower limit of protein intake recommended in current guidelines (1.2 g/kg/day) [9, 10]. In contrast, participants in the intervention group will receive a higher protein intake of 1.8 g/kg/day. As described previously, both caloric and protein intake will be adjusted to remain within 100–110% of the prescribed targets. Although European Society for Clinical Nutrition and Metabolism guidelines suggest higher protein targets for selected populations, such as trauma or obese patients [9], the present trial is not designed to individualize protein prescription based on diagnostic subgroups, but rather to evaluate the effect of two predefined protein targets under standardized mobilization conditions. Randomization is expected to distribute such patient characteristics evenly between groups.

The core intervention period will continue from Day 3, when protocolized protein delivery is initiated, until ICU discharge, death, or the initiation of oral intake, whichever occurs first, for a maximum of 28 days from randomization. During this period, standardized high-intensity mobilization will be provided as part of routine ICU care to all eligible patients.

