### Randomization

Written informed consent will be obtained from patients who are expected to require mechanical ventilation for > 48 h. Once consent is obtained, randomization will be performed. The consent process will be completed within 24 h of initiating mechanical ventilation.

Randomization will be conducted using a variable block method, with block sizes of four, six, or eight selected at random, and patients will then be allocated to the two groups in a 1:1 ratio. Allocation will be performed by an independent third party who is not involved in clinical care or data analysis. To ensure allocation concealment, clinical staff will be informed of the assigned group only after patient enrollment.

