### Data collection

Baseline characteristics will be collected at the start of the intervention, and will include demographic and clinical data: age, sex, body mass index, primary diagnosis, and comorbidities assessed using the Charlson Comorbidity Index [26]. Severity of illness will be measured using the Acute Physiology and Chronic Health Evaluation (APACHE) II score. Additional clinical variables will include the presence of acute kidney injury (AKI) according to the Kidney Disease: Improving Global Outcomes criteria [27], presence of diabetes, score on the Malnutrition Universal Screening Tool [28], and the presence of malnutrition defined by the Global Leadership Initiative on Malnutrition criteria [29]. Furthermore, body composition will be assessed at enrollment using a bioelectrical impedance analyzer (InBody BWA2.0S; InBody Japan, Tokyo, Japan) to determine parameters including skeletal muscle mass, skeletal muscle index, fat-free mass index, and phase angle. Baseline FIM scores will not be collected because most patients are unable to undergo functional assessment at ICU admission due to sedation, mechanical ventilation, or impaired consciousness. Therefore, FIM was assessed only at hospital discharge, consistent with the study objective of evaluating post-ICU functional recovery.

Nutritional data will include the number of days from admission to initiation of enteral nutrition, the number of days until the target protein dose was achieved, and the mean intake of caloric, protein, parenteral caloric, enteral caloric, parenteral amino acid, and enteral protein during the intervention period. These data will be analyzed separately for Days 0–1 and from Day 3 onward.

Rehabilitation-related data will include the number of days from admission to initiation of mobilization, number of days mobilization was performed, and the ICU Mobility Scale score at ICU discharge [30].

In addition, treatment-related data will include the use of renal replacement therapy, use of ECMO, and the duration of mechanical ventilation.

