### Statistical analyses

After data collection is complete, continuous variables will be presented as mean ± SD or as median with interquartile range (IQR), and categorical variables as numbers with percentages. Baseline characteristics and study outcomes will be compared between groups using the Student’s t-test or Mann–Whitney *U* test for continuous variables, and the chi-square test or Fisher’s exact test for categorical variables. All outcome analyses will be conducted according to the intention-to-treat principle.

The primary analysis will compare outcomes between groups according to the intention-to-treat principle.

As a sensitivity analysis, analysis of covariance (ANCOVA) will be performed to explore the robustness of the primary findings to variability in intervention implementation. As the actual duration of high-protein nutrition and high-intensity mobilization may vary among participants despite randomization, these variables will be included as covariates to account for differences in intervention exposure rather than to adjust the primary treatment effect.

Covariates included in the ANCOVA will be pre-specified based on clinical relevance and trial design considerations, not selected in a data-driven manner. Importantly, these analyses are intended as exploratory sensitivity analyses to aid interpretation of the results and will not replace the primary intention-to-treat comparisons.

Furthermore, sensitivity analyses will be performed with adjustment for the presence of acute kidney injury and use of renal replacement therapy (RRT).

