This study is designed as a participant- and assessor-blinded randomized controlled trial, in which patients will remain blinded, while outcome assessors will also be blinded to group allocation to ensure reliability of the results. Another notable feature is the use of individualized caloric prescriptions based on REE measured through indirect calorimetry. This approach minimizes the risk of metabolic complications associated with overfeeding while ensuring appropriate nutritional management. Moreover, by balancing caloric targets with protein goals and employing an automated VBA-based calculation tool to determine formula and supplemental products, the study will enhance both precision and reproducibility in nutrition planning.

Several potential limitations should also be acknowledged. First, this is a single-center study, which may limit the generalizability of the findings. The single-site design was chosen for practical reasons, as relatively few ICUs are currently equipped with MPL, and its use requires specialized training. Second, the participant- and assessor-blinded design cannot completely eliminate the risk of treatment bias. To mitigate this concern, assessor blinding has been incorporated to minimize potential bias in outcome evaluation. Third, the duration of the intervention may vary among patients, with longer exposure potentially leading to greater functional improvement. To address this, ANCOVA including intervention duration as a covariate will be performed, and planned subgroup analyses will further account for potential heterogeneity.

Although recent post-hoc analyses have suggested potential harm of higher protein intake in patients with severe AKI [13], current guidelines do not recommend routine protein restriction.

Our protocol incorporates daily renal monitoring, predefined safety-driven adjustments, and planned subgroup analyses to address this concern.

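### The sensitivity analysis adjusted for RRT use has no time limit on RRT, so it can adjust away part of the protein effect; limit the covariate to baseline status

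*Protocol article*

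**What the plan says.** After describing the intention-to-treat comparison and an exposure-duration ANCOVA, the Statistical analyses section of the protocol article adds: "Furthermore, sensitivity analyses will be performed with adjustment for the presence of acute kidney injury and use of renal replacement therapy (RRT". It does not say which period of RRT use counts.

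Data collection treats the two covariates differently. AKI stands in the paragraph that opens "Baseline characteristics will be collected at the start of the intervention": "Additional clinical variables will include the presence of acute kidney injury (AKI) according to the Kidney Disease: Improving Global Outcomes criteria". RRT has a later paragraph of its own: "In addition, treatment-related data will include the use of renal replacement therapy, use of ECMO, and the duration of mechanical ventilation". Duration of ventilation, in the same list, is known only after allocation.

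Allocation is early. Under Randomization, consent is completed within 24 h of starting ventilation, and "Once consent is obtained, randomization will be performed". The protein contrast comes later. Under Interventions, "The core intervention period will continue from Day 3, when protocolized protein delivery is initiated", and it may last up to 28 days from randomisation.

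On renal risk, the Discussion notes that "recent post-hoc analyses have suggested potential harm of higher protein intake in patients with severe AKI". The Background mentions possible harm of higher protein in some contexts. The Nutrition protocol lets the attending physician change protein delivery when renal function deteriorates. RRT is not among the safety outcomes listed under Outcome.

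**The concern.** A sensitivity analysis of a randomised comparison should estimate the same effect as the primary analysis under a different assumption. Adjusting for something that happens after allocation and may depend on the arm changes the effect being estimated, in two ways.

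- **Mediation.** If a higher dose leads to more RRT, and RRT (or the renal failure it marks) goes with worse function, holding RRT fixed removes that part of the effect.
- **Selection.** If unmeasured severity drives both RRT and function, patients with the same RRT status in the two arms are not alike. The arm with more RRT will have a less severe mix within each RRT stratum, and so look better than it is.

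At stake is how readers interpret this analysis. An attenuated or reversed estimate could be taken as reassurance about the renal question that the protocol itself raises.

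**Working it through.** **Plan's own figures.** The plan gives no figure for this analysis. Its sample size section supplies the yardsticks: SD 20, difference 17, two-sided alpha 0.05, and 0.95 read as power. The exact two-sample t calculation gives power 0.945 at 36 per group and 0.950 at 37, so the stated 37 is reproduced. Allowing for 15% dropout, 37/0.85 = 43.5, so 44 per group or 88; the plan sets 90, or 45 per arm.

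**Step 1: does the covariate include RRT after allocation?** As written, yes. RRT is grouped with treatment data, AKI with data from the start of the intervention, and no section limits RRT to an earlier time.

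**Step 2: what adjustment does.** For least squares,

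adjusted difference = unadjusted difference − b × (p_high − p_usual),

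where p is the proportion with RRT in each arm and b is the fitted RRT coefficient. Suppose protein acts only through RRT, and RRT changes FIM motor by d. The total effect is then d × (p_high − p_usual). With no common cause of RRT and FIM, b = d and the adjusted difference is 0. With a severity factor that raises RRT use and lowers FIM, b is more negative than d, and the adjusted difference is (d − b) × (p_high − p_usual), which is positive when p_high exceeds p_usual.

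**Step 3: size under assumed inputs.** RRT rates, d and the severity link are all assumptions. In a simulation of 2,000,000 patients per scenario there is no direct protein effect and the FIM SD is about 20. Where severity acts, its latent correlation with RRT is 0.5 and it lowers FIM by 8 points per SD.

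| RRT, usual v high | d | Severity lowers FIM | Unadjusted | b | Adjusted |
|---|---|---|---|---|---|
| 15% v 25% | −10 | no | −0.97 | −10.01 | +0.02 |
| 15% v 30% | −20 | no | −2.94 | −19.97 | +0.03 |
| 15% v 25% | −10 | yes | −1.02 | −16.99 | +0.67 |
| 15% v 30% | −20 | yes | −2.95 | −26.95 | +1.09 |
| 15% v 30% | 0 | yes | +0.02 | −6.92 | +1.05 |
| 15% v 15% | −20 | yes | +0.03 | −27.3 | +0.02 |

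Check on the fourth row: −2.95 + 26.95 × 0.15 = −2.95 + 4.04 = +1.09.

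A second simulation used a logistic model for RRT on arm and severity, and FIM = 60 + d × RRT − 8 × severity + residual with SD 17. With d = −20, 16% v 29% took −2.63 to +0.85, and 13% v 33% took −3.92 to +1.34. With d = 0 the same rates gave +0.87 and +1.34 from selection alone, and a stronger severity link (19% v 31%) gave +1.38. A small difference in RRT, 16% v 19% with d = −20, took about −0.6 to about +0.2.

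**Step 4: against sampling error.** With 45 per arm and SD 20, SE = 20 × √(2/45) = 4.2. In the second model, √(17² + 8²) = 18.8 and 18.8 × √(2/45) = 4.0. A shift of 0.9 to 1.4 is therefore about a quarter to a third of one SE. With no true effect, the chance of a significant result favouring high protein rises from 2.5% to about 4 to 5.5%.

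**The case against.** - **Only a sensitivity analysis is affected.** This stands. The unadjusted intention-to-treat comparison remains primary and would be reported in any case. A reader might infer that the trial's main answer could lose a renal harm; the documents do not support that.
- **The causal step is inferred.** This stands too. The Discussion sentence concerns harm in patients who already have severe AKI, which is effect modification. No section says that a higher dose increases RRT use. The path is plausible given the renal concerns and the foreseen deterioration, but it is a condition of the finding, not a fact from the protocol.
- **No purpose is stated.** A reader might infer that the analysis is meant to rule out renal explanations and would hide the harm it examines. The section gives no reason for the adjustment. Renal harm also has other outlets: discharge creatinine and maximum blood urea nitrogen are safety outcomes, and deaths before hospital discharge score the minimum FIM.
- **The timing may be left to an analysis plan.** This does not remove the point. The covariate is already named, and the only description of how it is recorded places it with on-treatment data.
- **The duration ANCOVA and RRT subgroup share the root cause.** Conditioning on post-allocation variables is common to all three, but correcting the other two leaves this sentence as it is.

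**Conclusion.** The point holds as a minor-to-moderate defect of a sensitivity analysis. Followed as written, the analysis adjusts for RRT that may begin after allocation. It then estimates the total effect with bias if protein dose changes RRT use. Under the assumed rates of roughly 15% v 25 to 33%, a true harm of about 1 to 4 FIM motor points becomes about 0 to +1.3. With no difference in RRT use between arms, the bias is about zero.

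The shift is small beside both the standard error of about 4 and the 17-point design difference, so a spurious significant benefit is unlikely. The concern is the direction of the shift, which is towards reassurance. It applies to RRT, not to AKI, which is listed with the baseline data. RRT already under way before allocation is a legitimate covariate.

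**What to change.** In Statistical analyses, state that this sensitivity analysis adjusts only for AKI and RRT status at baseline. The preferred time point is randomisation, because treating staff learn the assigned group after enrolment. At the latest it should precede the start of protocolised protein delivery on Day 3. Use the same time point for the AKI variable in Data collection, where the start of the intervention should be tied to a specific day.

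Do not use RRT started after that point as a covariate. Report it by arm as a safety result and add it to the safety outcomes under Outcome.

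The cost is a sentence or two and extraction of the RRT start date from the medical record. The downside is that baseline RRT may be rare, so the adjustment may change little.

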### Outcome

The primary outcome will be the total motor domain score of FIM at hospital discharge. The FIM motor score at hospital discharge was selected as the primary outcome because it represents the earliest clinically stable time point at which the cumulative effects of ICU-based interventions can be meaningfully assessed. FIM at ICU discharge may be influenced by non-clinical factors such as bed availability and transfer policies, and may underestimate functional recovery due to ongoing critical illness and sedation effects. In contrast, longer-term follow-up after discharge is more susceptible to loss to follow-up and confounding by post-ICU rehabilitation and social factors. Therefore, assessment at hospital discharge was considered the most appropriate balance between clinical relevance, feasibility, and internal validity.

Secondary outcomes and their assessment time points will be as follows:At ICU discharge: Functional Status Score for the ICU [31], Medical Research Council (MRC) score, and ICU length of stay.At 14 days after ICU discharge: FIM motor, cognitive subscale of FIM (FIM cog), Mini-Mental State Examination (MMSE), body composition parameters, MRC score, and Brief Pain Inventory (BPI).At hospital discharge: MRC score, FIM cog, body composition parameters, BPI, length of hospital stay, and mortality.At 60 days after hospital discharge: FIM motor score, MRC score, FIM cog, MMSE score, body composition parameters, and BPI.

Follow-up at 60 days post-discharge will be conducted during an outpatient visit scheduled at the time of discharge. For patients who die or cannot be assessed owing to severe consciousness disturbance, the FIM motor and FIM cog will be recorded at their minimum values (13 and 5, respectively), the MRC score will be assigned as 0, and the BPI will be recorded as missing. For patients who die before hospital discharge, FIM scores will be assigned as the minimum possible values (motor score 13 and cognitive score 5). This approach reflects that death represents the worst possible functional outcome and ensures that mortality is appropriately incorporated into the analysis of functional recovery rather than treated as missing data.

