For all analyses, missing data will be addressed under the assumption of missing at random using multiple imputation. Given the possibility of non-random loss to follow-up after hospital discharge, sensitivity analyses exploring departures from the missing-at-random assumption (e.g., pattern-mixture or delta-adjustment approaches) will be conducted, and the extent and patterns of missingness will be reported. Variables related to missingness or outcomes—including group allocation, age, sex, Glasgow Coma Scale, ICU length of stay, and APACHE II score—will be incorporated in the imputation model. The specification of the imputation model will be informed by assessment of missing data patterns and inter-variable associations to ensure model adequacy. This approach will also be applied to post-discharge follow-up outcomes, including those assessed at 60 days, to account for missing data due to transfer or loss of contact.

Model assumptions for ANCOVA will be evaluated using standard diagnostic procedures, including inspection of residual distributions and assessment of homoscedasticity. If major violations are identified, appropriate transformations or robust alternatives will be considered and reported.

No interim analyses will be conducted. All statistical analyses will be performed using R (version 4.5.0), and all statistical tests will be two-sided. Statistical significance will be set at 0.05 across all analyses.

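### As written, the plan imputes pain scores (BPI) for patients who have died: death leaves BPI missing, and missing data are imputed for all analyses

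*Protocol article*

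**What the plan says.** The protocol article deals with death in its Outcome section. For patients who die or cannot be assessed because of severely disturbed consciousness, "the FIM motor and FIM cog will be recorded at their minimum values (13 and 5, respectively"; in addition, "the MRC score will be assigned as 0, and the BPI will be recorded as missing". The reason given for the FIM rule is that it "ensures that mortality is appropriately incorporated into the analysis of functional recovery rather than treated as missing data".

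The same section lists secondary outcomes that have no rule for death:

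- FSS-ICU: "At ICU discharge: Functional Status Score for the ICU [31], Medical Research Council (MRC) score, and ICU length of stay".
- MMSE and body composition, 14 days after ICU discharge: "cognitive subscale of FIM (FIM cog), Mini-Mental State Examination (MMSE), body composition parameters, MRC score, and Brief Pain Inventory (BPI".
- MMSE and body composition again at the last visit: "At 60 days after hospital discharge: FIM motor score, MRC score, FIM cog, MMSE score, body composition parameters, and BPI".

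Body composition is also measured at hospital discharge.

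The Statistical analyses section sets the missing-data method: "For all analyses, missing data will be addressed under the assumption of missing at random using multiple imputation". It adds: "This approach will also be applied to post-discharge follow-up outcomes, including those assessed at 60 days", and gives transfer and lost contact as the causes of missingness it has in mind there. It also places every outcome analysis under the intention-to-treat principle.

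**The concern.** Multiple imputation under missing at random presumes that a value exists and was merely not observed. A dead patient has no pain score, so there is nothing for the model to recover. An imputed BPI for that patient refers to a hypothetical world in which the patient survived, which is not a question the trial sets out to answer.

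The result would also be hard to read. A BPI comparison would appear to cover all randomised patients when an unknown share of its values belongs to the dead. One patient could carry FIM cog 5 and MRC 0 for death beside an imputed pain score at the same time point. BPI is among the secondary outcomes named in the abstract, so the comparison is likely to be reported. Deaths are foreseeable: the trial enrols patients expected to need at least 48 h of ventilation, admits patients on ECMO, and lists mortality as an outcome.

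**Working it through.** **The plan's own figure.** The total of 90 serves here only as a denominator. With a difference of 17, an SD of 20, two-sided alpha 0.05 and the stated β of 0.95 read as power, the normal approximation gives n per group = 2 × (1.960 + 1.645)² / (17/20)² = 2 × 12.996 / 0.7225 = 35.97, so 36. The t-test version gives 36.96, so 37, as stated. Then 74 / 0.85 = 87.1, or 88 for equal groups, and the plan sets 90. The sample size reproduces, and the present point does not depend on it.

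**Outcomes against the death rule.** Each outcome in the Outcome section is set against the rule for death there and the imputation rule in Statistical analyses.

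| Outcome | When assessed | Value at death | Under the imputation rule |
|---|---|---|---|
| FIM motor (primary at hospital discharge) | 14 days after ICU discharge, hospital discharge, 60 days | 13 | Not missing, not imputed |
| FIM cog | 14 days after ICU discharge, hospital discharge, 60 days | 5 | Not missing, not imputed |
| MRC | ICU discharge and the three later points | 0 | Not missing, not imputed |
| BPI | 14 days after ICU discharge, hospital discharge, 60 days | Explicitly missing | Imputed |
| MMSE | 14 days after ICU discharge, 60 days | None given | Imputed, by inference |
| FSS-ICU | ICU discharge | None given | Imputed, by inference |
| Body composition | 14 days after ICU discharge, hospital discharge, 60 days | None given | Imputed, by inference |

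For BPI, two explicit statements meet: one makes the value missing, the other imputes missing values without exception. For the last three rows only the general rule is explicit.

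**Does other text remove the problem?**

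- The sensitivity analyses for departures from missing at random are motivated by loss to follow-up after hospital discharge, not by death.
- Survival status is not among the named imputation variables, although that list is not exhaustive.
- The intention-to-treat statement gives no support for an unstated survivor-only set.

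**Number of patients.** The documents give no mortality rate, so the range is an assumption. Patients concerned = 90 × mortality before the assessment:

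- 10%: 90 × 0.10 = 9
- 20%: 90 × 0.20 = 18
- 30%: 90 × 0.30 = 27
- 40%: 90 × 0.40 = 36

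The applicable rate differs by time point: for FSS-ICU it is mortality in the ICU, for the 60-day outcomes it also includes deaths after discharge.

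**The case against.** The strongest reply is that the authors never meant to impute for the dead. Recording BPI as missing may simply have meant leaving those patients out, and the sentence on post-discharge outcomes names transfer and lost contact, which describe living patients. This softens the literal reading at 60 days. It does not settle the matter, because death is not excluded there and BPI is also assessed 14 days after ICU discharge and at hospital discharge, where only the unqualified general sentence applies.

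A second reply is that a condensed article may leave the handling of death for MMSE, FSS-ICU and body composition to an analysis plan that is not shown. That stands. For these outcomes the point is an inference from the general rule. For BPI it is not, because the article itself fixes both rules.

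A third reply is that the harm is not demonstrated. This also stands in part. The imputation model contains group allocation, APACHE II, Glasgow Coma Scale, age and ICU stay, so values would be drawn conditional on arm and severity. The estimate could resemble a covariate-adjusted comparison of survivors, and a survivor-only analysis would share its dependence on who survives. The gain is a defined and honestly labelled comparison, not a proven change in the estimate.

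A reader might also infer that the plan breaks its own principle that death is not missing data. The stated reason concerns FIM and functional recovery; it makes no claim about pain or body composition.

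**Conclusion.** The point holds for BPI on the text as written: the stated rules produce pain scores for dead patients. It extends to MMSE, FSS-ICU and body composition only by inference. It is of moderate weight and touches secondary outcomes only. Its size is about 9 to 36 of 90 patients under an assumed 10% to 40% mortality; the documents allow nothing firmer.

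Four stronger readings are tempting and not supported:

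- That the primary result is compromised. FIM motor is fixed at 13 for deaths and is not imputed.
- That cognition as a whole is affected. FIM cog is fixed at 5; only MMSE is exposed.
- That deaths make up all the BPI missingness not caused by loss to follow-up. Living patients with severely disturbed consciousness also have BPI recorded as missing.
- That the arm with more deaths would be favoured. The direction and size of any bias depend on the imputation model and on mortality by arm, and neither can be determined from the documents.

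**What to change.** In Statistical analyses, or in the analysis plan if it is still open, add the following:

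1. Multiple imputation is applied only to patients alive at the assessment time concerned.
2. BPI and body composition are reported among survivors, with the number alive per arm beside each result and a label saying that the comparison is conditional on survival.
3. For MMSE and FSS-ICU, a rule for death is pre-specified. Worst value or worst rank would match the FIM and MRC rule; a survivor-only report is an acceptable alternative.
4. The handling of BPI in living patients who cannot be assessed because of severely disturbed consciousness is stated. Item 1 alone would still have their pain scores imputed.

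The cost is a few sentences and no new data. No interim analysis is planned, and no participant had been enrolled when the article was submitted, so a dated change before any comparison by arm should be straightforward. The downside is small: the BPI and body-composition comparisons, and any other outcome reported in survivors, become explicitly survivor-only and lose the full protection of randomisation.
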